#### Primary Outcome Analysis

The main analysis will be carried out according to the intention-to-treat principle (ITT), considering all patients who have started the substitution treatment with injectable depot buprenorphine. The primary outcome measure is the difference of OSTQOL (20) scores between baseline (t_0_) and month 12 (t_4_) in the depot group. The average OSTQOL mean score will be compared between these time points and analyzed for statistical significance using dependent *t*-tests. It is tested against the statistical null hypothesis (H0) of a decrease or no change in the OSTQOL mean score. The alternative hypothesis (H1) consists in a significant improvement of the OSTQOL mean score, which corresponds to an improvement in quality of life of the patients.

H0: M (Month 12) ≤ M (baseline) (OSTQOL mean score at 12 months ≤ baseline OSTQOL mean score)H1: M (Month 12) > M (baseline) (OSTQOL mean score at 12 months > baseline OSTQOL mean score).

The hypothesis will be tested two-sided at a significance level of *p* < 5%. The statistical analyses will be made according to the intention-to-treat (ITT) as well as to the per-protocol (PP) principle. The PP sample is defined by all patients who have undergone OST with injectable subcutaneous depot buprenorphine for at least 12 months and for whom sufficient baseline and 12-month data are available. The ITT sample comprises all patients who provided a written consent, who have undergone the baseline assessment, and–for patients in the depot study arm–who have received the first dose of injectable depot buprenorphine. For the ITT analysis, data from all study patients will be used independently of their status in or out of treatment with injectable depot buprenorphine. Missing values at the 12-month time point will be replaced by missing imputation procedures. These may either include last observation carried forward (LOCF) approaches or longitudinal mixed model analyses using all available follow-up assessments. The choice of imputation procedures for the ITT analysis will depend on the proportion of missing values at the 12-month time point as well as the quantity of available data at 3-month and 6-month follow-up, and will be determined by sensitivity analyses.

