### Sample Size Calculation

A study by Apelt et al. (30) showed a significant improvement in health-related quality of life (measured by SF-36) with an average effect size of *d* = 0.40 after 12 months among patients who switched from (levo-) methadone or buprenorphine to buprenorphine/naloxone. A study by Karow et al. (31) found effect sizes in the improvement of quality of life measured by MSQOL in patients treated with diamorphine between *d* = 0.73 (after 6 months) and *d* = 0.80 (after 12 months).

An α-error of 5% and a statistical power of 80% (β-error = 20%) will be used. In our study we anticipate a smaller effect size of d = 0.25 which will result in a minimum number of *N* = 128 patients. Further we estimate a drop-out rate of 40% until month 12 (t_4_) resulting in a sample size of *N* = 213 patients treated with injectable depot buprenorphine. Considering the same number of patients in the matched control group, the total sample size is *N* = 426. Under the conditions of an α-error of 5% and a statistical power of 80% this sample size allows for detection of statistically significant differences in group comparisons with an effect size of *d* = 0.35 or higher.

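### The primary missing-data method is left open between LOCF and a mixed model and may be chosen by results; with 40% planned drop-out, LOCF answers a different question from change at month 12

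*Protocol article*

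**What the plan says.** The primary endpoint is the change in OSTQOL from baseline to month 12 within the depot arm, tested by a dependent t-test in the ITT sample (Primary Outcome Measure; Primary Outcome Analysis). Missing month-12 values are to be replaced. On the procedures, the article says: "These may either include last observation carried forward (LOCF) approaches or longitudinal mixed model analyses using all available follow-up assessments". On the selection between them, it says: "The choice of imputation procedures for the ITT analysis will depend on the proportion of missing values at the 12-month time point". It adds the amount of data at months 3 and 6 as a second criterion and closes with "and will be determined by sensitivity analyses". No default, cut-off or decision rule is given.

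Three other places bear on this:
- Sample Size Calculation plans for 40% drop-out by month 12, that is 128 evaluable out of 213 depot patients.
- Table 2 schedules OSTQOL at baseline and months 3, 6 and 12, but not at month 1.
- Drop-Outs excludes patients who cannot be analysed and gives missing baseline and follow-up data as an example.

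**The concern.** A sensitivity analysis should test a primary result that is already fixed. Here it may select that result. If both candidate analyses are run in order to decide, both p-values are visible before the choice is made.

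The two candidates also estimate different things. The mixed model estimates the mean change to month 12. LOCF followed by a t-test estimates the mean change to whichever visit was last observed. Because there is no month-1 OSTQOL, a patient lost before month 3 is entered as no change at all, unless the Drop-Outs section is read as removing that patient. A patient lost later has a month-3 or month-6 score counted as a month-12 score. The primary comparison is within one arm, so no control group offsets the bias.

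**Working it through.** **The plan's own figures.** Inputs from Sample Size Calculation and Primary Outcome Analysis: α = 0.05 two-sided, power 80%, d = 0.25.
- Normal approximation: (1.960 + 0.842)² / 0.25² = 125.6, so 126. The noncentral t gives 128 (power 0.8015), which matches the article. A one-sided test would need 101, so the stated figure is two-sided.
- Inflation: 128 / 0.6 = 213.3, which matches 213.
- Expected missing at month 12: 0.40 × 213 = 85.

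**Assumptions, because the article gives no drop-out timing or trajectory.** Losses of 15% before month 3, 12% between months 3 and 6, and 13% between months 6 and 12. Correlation r = 0.6 between any two visits. Losses unrelated to outcome. Unit: the SD of one OSTQOL score. The SD of a change is then √(2 × (1 − 0.6)) = 0.894, and the planning effect is 0.25 × 0.894 = 0.224 SD.

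**What LOCF estimates.** With true mean gains m3, m6 and m12:

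expected LOCF change = 0.15 × 0 + 0.12 × m3 + 0.13 × m6 + 0.60 × m12

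**Standard errors.**
- LOCF: √(0.85 × 0.8 / 213) = 0.0565. Simulation: 0.056 reported, 0.057 actual sampling SD.
- All 213 truly observed: √(0.8 / 213) = 0.061.
- 128 completers: √(0.8 / 128) = 0.079.
- Mixed model, simulated: 0.074.

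**Gains that fade by month 12 (true month-12 change zero).** The upper-tail rejection rate is approximately P(Z > 1.96 − estimate / 0.0565).

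| True gain at months 3 / 6 / 12 | Expected LOCF estimate | Shift | Approx. | Simulated |
|---|---|---|---|---|
| 0.30 / 0.20 / 0 | 0.036 + 0.026 = 0.062 | 1.10 | 19% | 20% |
| 0.30 / 0.30 / 0 | 0.036 + 0.039 = 0.075 | 1.33 | 26% | 26–28% |
| 0.22 / 0.15 / 0 | 0.026 + 0.020 = 0.046 | 0.81 | 13% | 12% |
| 0.15 / 0.10 / 0 | 0.018 + 0.013 = 0.031 | 0.55 | 8% | 8% |

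In the first two rows the simulated mixed model rejects in 2.4% to 3.1% (nominal 2.5%). With last visits split equally over months 0, 3 and 6, a gain at the planning effect held to month 6 and gone by month 12 gives LOCF 18% and the mixed model 2.6%.

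**Gains that hold or build to 0.224.**
- Steady: 0.85 × 0.224 = 0.19.
- Linear (0.056, 0.112, 0.224): 0.0067 + 0.0146 + 0.1344 = 0.16.

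**If patients lost before month 3 are excluded** (0.85 × 213 = 181 remain). The first table row becomes 0.062 / 0.85 = 0.073 with SE √(0.8 / 181) = 0.0665, so the shift stays at 1.10 and the false-positive rate hardly moves. A steady gain is then estimated without bias, a linear one at 0.156 / 0.85 = 0.18. The LOCF standard error no longer falls below 0.061.

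**Picking whichever method is significant.** With no change at any visit, simulated two-sided error is 6.5% (6.6% under the equal split).

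**Limits and power of the mixed model (equal split; units of the SD of change).** Suppose completers gain 0.25, and drop-outs show 0.25 while observed but end 0.375 below baseline. The overall change is 0.6 × 0.25 − 0.4 × 0.375 = 0. The mixed model estimates 0.25 and declares benefit in 85% of runs; LOCF estimates 0.22 and does so in 92%. With a steady true gain of 0.25 in everyone, the mixed model has about 84% power with 213 patients.

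**The case against.** The strongest reply is that an article may leave detail to an analysis plan, and that the two named criteria (proportion missing, amount of month-3 and month-6 data) can be judged without seeing any outcome. Much of that is fair. It does not dispose of the closing clause on sensitivity analyses, which is a stated selection rule rather than an omission.

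A reader might also infer more than the document supports:
- **That both results will certainly be known before the choice.** The clause permits this but does not say it.
- **That the LOCF standard error is about a quarter too narrow (0.056 against 0.074).** These belong to different estimands. The LOCF standard error agrees with its own sampling SD, and its t-test has nominal error when nothing changes at any visit. The fault is the wrong target: 0.056 lies below even the 0.061 of complete data, so as a statement about month 12 it claims too much.
- **That control of the 5% level is lost.** When nothing changes at any visit, the inflation is to about 6.5%.
- **That LOCF always flatters the treatment.** It understates a steady or rising gain. The one cited trajectory, from the diamorphine study, does not fade (d = 0.73 at 6 months, 0.80 at 12), though the treatment and instrument differ.
- **That a mixed model cures the problem.** It fails too if drop-outs worsen after their last visit.

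The 85 missing values are also a planning figure. Selection and Treatment of Participants and Assessment and Timelines keep patients in follow-up after treatment ends, so the loss could be smaller.

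**Conclusion.** The concern holds in this form. The method behind the primary p-value is not fixed, the text allows results to influence it, and one of the two candidates does not estimate the stated endpoint. At the planned 40% drop-out, LOCF gives 12% to 28% false claims of improvement against 2.5% nominal when early gains of 0.22 to 0.3 SD vanish by month 12. A true gain of about 0.22 SD is estimated at about 0.19 if steady and 0.16 if rising. These sizes are illustrative. They rest on the assumed timing, r = 0.6 and the assumed trajectories, and the steady-gain shortfall also depends on keeping patients lost before month 3 in the analysis. That the choice is open, and that LOCF has the wrong target, follow from the article's own text and visit schedule.

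**What to change.** Before any outcome data are reviewed:
1. Name one primary analysis: a likelihood mixed model for repeated measures on depot-arm OSTQOL at baseline and months 3, 6 and 12, with the month-12 minus baseline contrast as the primary estimate. Multiple imputation from the same visits followed by the paired test would also serve.
2. Remove LOCF as an option for the primary analysis.
3. State that sensitivity analyses cannot change the primary method. Prespecify delta-adjusted (missing-not-at-random) analyses, because the mixed model is itself exposed if drop-outs deteriorate.
4. State whether a patient with a baseline but no later OSTQOL stays in the ITT set. Reconcile the Drop-Outs section, which counts ending OST as drop-out, with the sections that continue follow-up after OST ends.

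Cost: a paragraph of analysis text, a model in place of the simple paired t-test, some added analysis work, and a wider interval (SE about 0.074 SD instead of 0.056). No extra visits are needed. Under the assumptions above no extra patients are needed either, since power is about 84% at a steady gain equal to the planning effect.

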#### Secondary Outcome Analyses

Secondary data analyses will be carried out in accordance with the scale levels of the variables or scores and indices (drug consumption, somatic or mental health symptoms, quality of life, withdrawal symptoms, craving, treatment satisfaction) and along the expected relationships between individual variables, e.g., in the context of bivariate or multivariate analyses. Comparisons between depot patients and matched control group will be done by a mixed model approach with baseline OSTQOL score and the (pairwise) cluster term as covariates and will include all follow-up measurement points, such as month 3 and month 6 (see Table 2). Retention rates will be analyzed using descriptive statistics. For group comparisons, Chi^2^-tests (percentages) as well as Kaplan-Meier survival methods and Log-Rank Tests will be used. The significance level will be defined at *p* < 5%.

**Table 2 T2:** Overview of outcome domains, instruments and measurement.

**Outcome domain**	**Instrument**	**t_**0**_**	**t_**1**_**	**t_**2**_**	**t_**3**_**	**t_**4**_**
Quality of life	OSTQOL	x		x	x	x
Acceptance	TSQM-14	x	x	x	x	x
Patient satisfaction with	CSQ-8	x	x	x	x	x
OST care						
Dosage adequacy	ODAS	x	x	x	x	x
Substance use	EuropASI, Urine samples	x	x	x	x	x
Psychological distress	BSI-18	x			x	x
Social participation	Self-constructed questionnaire	x			x	x
Retention	CRF		x	x	x	x
Cost-effectiveness	EQ-5D	x			x	x
Health	OTI-HSS	x			x	x
Adverse events	AE, SAE, ADR	If necessary				

*t_0_, baseline; t_1_, month 1; t_2_, month 3, t_3_, month 6 and t_4_, month 12; OSTQOL, Opioid Substitution Treatment Quality of Life scale; TSQM-14, Treatment Satisfaction Questionnaire for Medication; CSQ-8, Client Satisfaction Questionnaire; ODAS, Opiate Dosage Adequacy Scale; EuropASI, European Addiction Severity Index; BSI-18, Brief Symptom Inventory 18; CRF = Case-Report Form; EQ-5D, EuroQOL five dimensions questionnaire; OTI-HSS, Opiate Treatment Index-Health Symptom Scale; AE, adverse event; SAE, serious adverse event; ADR, adverse drug reaction*.

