## Abstract

**Introduction:** Once-weekly or once-monthly injectable depot buprenorphine is a new opioid substitution treatment (OST) medication that provides clinically relevant plasma concentrations without daily peaks. Together with a high tolerability and acceptance reported by patients, the prolonged release of injectable depot buprenorphine might have beneficial implications on the patients' quality of life and social participation. The primary objective of this prospective non-interventional observational study is to evaluate the effects of subcutaneous injectable depot buprenorphine on the quality of life of patients in routine OST care in Germany. Secondary outcomes like illicit substance use, psychological distress, social participation and activity are assessed to provide an overall evaluation toward addiction recovery.

**Methods and Analysis:** The present study is a non-randomized prospective observational study with a control group (treatment-as-usual). To ensure comparability between both patient groups, suitable control patients (*n* = 213) from the same OST unit will be matched pairwise to each patient treated with injectable depot buprenorphine (*n* = 213). Matching variables are gender, duration of OST, take-home prescription and psychosocial functioning (according to the Global Assessment of Functioning scale). Primary study endpoint is the difference of change in quality of life, assessed with the recently developed Opioid Substitution Treatment Quality of Life scale (OSTQOL), within the depot buprenorphine group between baseline and month 12. The primary analysis will be carried out according to the intention-to-treat principle (ITT) by comparing OSTQOL mean scores using dependent *t*-tests. For secondary analyses, group comparisons will be done by mixed model approaches with baseline OSTQOL score and the (pairwise) cluster term as covariates.

**Discussion:** The study combines clinical, routine OST care data with relevant patient reported outcome data. The pairwise matching allows conclusions on effects of different OST medications. The study findings will provide new insights in the addiction recovery processes of OST patients treated with depot buprenorphine.

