### Secondary Outcome Measures

Secondary endpoints include the difference in the OSTQOL score between depot and control group at month 12 (t_4_), comparisons between the depot and control group in patient satisfaction (Client Satisfaction Questionnaire–CSQ-8) at month 12 (t_4_), substance use (i.e., on the basis of self-reporting) at month 6 (t_3_) and month 12 (t_4_), the retention rate in treatment at month 12 (t_4_), psychological distress (Brief Symptom Inventory 18) at t_4_, social participation at month 6 (t_3_) and month 12 (t_4_) as well as the cost-effectiveness (on the basis of quality-adjusted life years (QALYs); EuroQOL five dimensions questionnaire (EQ-5D) at month 12 (t_4_). Three secondary endpoints will be measured solely in the depot group, the acceptance of the depot medication and its application measured by the Treatment Satisfaction Questionnaire for Medication (TSQM-14) at month 1, 3, 6 and 12 (t_1_-t_4_), the dosage adequacy measured by the Opiate Dosage Adequacy Scale (ODAS) at month 1, 3, 6 and 12 (t_1_-t_4_) and changes in quality of life domains (OSTQOL subscales) in depot group over time between baseline (t_0_) and month 12 (t_4_). Possible adverse reactions will be assessed by a physician and recorded as part of the documentation of adverse events (AEs) and adverse drug reactions (ADRs). An overview of all primary and secondary outcome measures is provided in Table 1.

**Table 1 T1:** Overview of primary and secondary outcome measures.

**Primary outcome measure**	**Difference of OSTQOL total score in depot group between baseline (t_0_) and month 12 (t_4_)**
**Secondary outcome measures**	1. Quality of life (OSTQOL score) between depot and control group at t_4_ 2. Acceptance (TSQM-14) of injectable depot buprenorphine between t_1_ and t_4_ 3. Patient satisfaction with OST care (CSQ-8) between depot and control group at t_1_- t_4_ 4. Dosage adequacy (ODAS) in depot group at t_1_-t_4_ 5. Substance use (i.e., self-reporting) between depot and control group at t_3_ and t_4_ 6. Psychological distress (BSI-18) between depot and control group at t_4_ 7. Social participation between depot and control group at t_4_ 8. Retention rate (percentage of patients) in depot group at t_3_ and t_4_ 9. Cost-effectiveness [on the basis of quality-adjusted life years (QALYs); EQ-5D] between depot and control group at t_4_ 10. Changes in quality of life domains (OSTQOL subscales) in depot group between baseline (t_0_) and month 12 (t_4_)

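### For between-group outcomes other than OSTQOL, the only baseline covariate named is OSTQOL, so differences in the outcome's own baseline are only partly corrected

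*Protocol article*

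**What the plan says.** Under Secondary Outcome Analyses the protocol article states: "Comparisons between depot patients and matched control group will be done by a mixed model approach with baseline OSTQOL score". The only other covariate it names is a term for the matched pair. It adds that the model "will include all follow-up measurement points, such as month 3 and month 6 (see Table 2"). The Abstract repeats the covariate set in general terms: "For secondary analyses, group comparisons will be done by mixed model approaches with baseline OSTQOL score and the (pairwise) cluster term as covariates". Neither place restricts the rule to one outcome, and neither names the baseline of the outcome being analysed.

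Secondary Outcome Measures lists the contrasts between the groups. One is OSTQOL itself: "Secondary endpoints include the difference in the OSTQOL score between depot and control group at month 12". The others include "Psychological distress (BSI-18) between depot and control group at t_4", as well as CSQ-8, self-reported substance use, social participation and cost-effectiveness from EQ-5D. Retention is handled separately, by Chi² tests, Kaplan-Meier curves and log-rank tests.

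Under Study Design, controls come from the same OST unit and are matched on gender, OST duration, take-home status and GAF. The Discussion concedes that patients who choose depot treatment may differ from others in severity and functioning.

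**The concern.** Without randomisation, a difference between the groups at t0 in, say, BSI-18 carries forward into the month-12 contrast to the extent that BSI-18 is stable over the year. The direct remedy is to condition on baseline BSI-18. Baseline OSTQOL is a proxy for it and removes only the part of the imbalance that the two measures share. None of these outcomes is a matching variable.

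Imbalance is plausible on the protocol's own account. Controls are patients who do not want to switch, and the Treatment section expects some depot patients to have had problems with their previous medication. Part of an apparent medication effect on distress, satisfaction or substance use could then be a difference that was already present at t0. The outcome's own baseline is also usually its best single predictor, so leaving it out widens the confidence intervals for no gain.

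**Working it through.** **The plan's own figures.** Two-sided 5%, 80% power, d = 0.25, paired t-test: (1.960 + 0.842)² / 0.25² = 125.6 by the normal approximation. The noncentral t gives 127.5, hence 128. Drop-out: 128 / 0.60 = 213.3, stated as 213. Between groups with 128 evaluable per arm: (1.960 + 0.842) × √(2/128) = 0.350. All three figures reproduce, and none depends on the covariate choice.

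**Which outcomes are touched** (Secondary Outcome Measures and Table 2):

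| Between-group outcome | Measured at t0 | Baseline OSTQOL is its own baseline |
|---|---|---|
| OSTQOL | yes | yes |
| CSQ-8 | yes | no |
| Substance use | yes | no |
| BSI-18 | yes | no |
| Social participation | yes | no |
| EQ-5D | yes | no |
| Retention | no baseline value | analysed outside the model |

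**Residual bias.** The documents give no correlations or gaps, so every input here is an assumption. In SD units:
- r is the correlation of the outcome at month 12 with its own baseline.
- ρ is the correlation of that baseline with baseline OSTQOL.
- d0 is the group gap in the outcome's baseline.
- g is the group gap in baseline OSTQOL.

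Suppose OSTQOL is related to the later outcome only through the outcome's baseline. The within-group slope on baseline OSTQOL is then rρ, and

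bias = r·d0 − r·ρ·g.

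If the OSTQOL gap follows the correlation (g = ρ·d0), this becomes r·d0·(1 − ρ²):
- Low end: 0.4 × 0.2 × (1 − 0.49) = 0.041 SD.
- High end: 0.7 × 0.3 × (1 − 0) = 0.21 SD.
- Middle case (r = 0.6, ρ = 0.5, d0 = 0.3): 0.18 SD unadjusted, 0.18 × 0.75 = 0.135 SD after OSTQOL adjustment, and 0 in this model after own-baseline adjustment.

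The share removed by OSTQOL is ρ²: 9% at 0.3, 25% at 0.5, 49% at 0.7. The result is sensitive to g. In the middle case, g = 0 leaves 0.18 SD and g = d0 leaves 0.6 × 0.3 × (1 − 0.5) = 0.09 SD.

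**Consequence in the middle case.** With 128 per arm, and ignoring within-pair correlation, the standard error is √(1 − 0.3²) × √(2/128) = 0.954 × 0.125 = 0.119. Bias over standard error is 0.135 / 0.119 = 1.13. The chance of a significant result with no true effect is then 0.205 instead of 0.05. With 213 per arm it is 0.309.

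**Precision.** With an own-baseline correlation of 0.6, the residual variance is 1 − 0.36 = 0.64. If baseline OSTQOL correlates 0.3 or 0.4 with the month-12 outcome, it is 0.91 or 0.84. The standard error ratios are √(0.91/0.64) = 1.19 and √(0.84/0.64) = 1.15.

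**The case against.** The best defence is that the sentence was meant for OSTQOL alone. It names baseline OSTQOL, and in Table 2 OSTQOL is the only instrument whose interim follow-ups are exactly months 3 and 6. BSI-18, social participation and EQ-5D have no month-3 visit, while CSQ-8 and substance use also have month 1. In the Abstract the sentence directly follows the OSTQOL primary analysis. This reading is possible, but the text does not state it. The months are given as examples, the reference is to a table covering all outcomes, and the Abstract speaks of group comparisons without limit.

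A second defence is that this is a condensed article, and outcome-specific covariates are commonly left to an SAP, which is not shown and may settle the matter. That would answer silence. Here a covariate set is named, twice, and it does not suit most of the outcomes it appears to cover.

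Third, same-unit matching and baseline OSTQOL, which has psychological stress and social contacts among its subscales, already remove some imbalance. That stands, and it is why the correction is partial and not absent.

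A reader might also infer that the pair term is a fixed covariate, so that pairs broken by the 40% drop-out contribute nothing. With independent drop-out only 213 × 0.6 × 0.6 ≈ 77 pairs would be complete, and the detectable effect would exceed 0.35. The documents do not support this. A cluster term in a mixed model is conventionally a random effect. The stated model also uses earlier visits, so a broken pair can still inform the month-12 contrast.

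**Conclusion.** The point holds for the modelled between-group outcomes other than OSTQOL. As written, they would be adjusted for another scale's baseline while their own collected t0 value goes unused. Under the assumptions shown, the remaining bias is about 0.04-0.21 SD. The middle value of 0.135 SD is more than a third of the stated detectable effect (0.135 / 0.35 = 0.39). The range rests on assumed correlations, an assumed baseline gap and an OSTQOL gap that follows the correlation. It shows what could happen and does not predict what this study will find.

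A reader might conclude that every depot-control comparison is affected, or that imbalance is left wholly uncorrected. Neither follows. For OSTQOL the named covariate is the right one, and retention lies outside the model. The primary endpoint is a change within the depot group and uses no such covariate. The change should be made, but it concerns secondary analyses only.

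**What to change.** In Secondary Outcome Analyses, and in the matching sentence of the Abstract, state that each modelled depot-control comparison is adjusted for the t0 value of the outcome analysed. Baseline OSTQOL may be kept as an optional extra covariate, and the pair term stays as the cluster (random) effect. Baseline OSTQOL alone then applies only to the OSTQOL comparison. If the sentence was always meant for OSTQOL only, say so and give the own-baseline rule for the other outcomes beside it. Adding the four matching variables to the model is optional.

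The cost is a change of wording. All the values needed are already scheduled at t0, and no visit, instrument or sample size figure changes. The rule should be fixed before the between-group data are analysed.
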